### Exploratory Endpoints:

Within individual change from Day 0 to Week +36 (i.e. treatment phase) in:

- ☐ Stool microbiome
- ☐ Adaptive behavior function: Vineland Adaptive Behavior Scales, Third Edition (VABS-III) – Day 0 to Week 3

## 10.0 Procedures Involved

### 10.1 Study design

This is an open label, single center, pilot study of 20 participants with MPS. There will be an initial screening visit, followed by an 8-week observational period, then a

36-week treatment period, and finally another 8-week observational period to determine any effects of withdrawal from the treatment. Total duration of subject participation is 52 weeks.

[figure not shown]

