### Secondary Endpoints:

Within individual change over 8-week treatment period (on maximum effective and tolerated dose) compared to change over 8-week observational period, and from Day 0 to Week +36 (i.e. treatment phase) in:

1. Incidence of treatment-emergent adverse events and laboratory values over 36-weeks of treatment to known frequency of anakinra-related AEs in other populations.
2. MDRI comprised of:
  - Sanfilippo Behavior Rating Scale (SBRS): Minimal Clinically Important Difference (MCID) = 0.25 SD for each scale
  - Child Sleep Health Questionnaire (CSHQ): MCID = 1-point change 
  - Autism Parenting Stress Index (APSI): MCID = 0.25 SD for Stress Total 
  - PROMIS Fatigue - Parent Proxy Custom Short Form: MCID = 3-point change
  - Movement disorder (e.g. dystonia, chorea, etc.): Parent reported duration and severity. Change in one of two characteristics for +/-1 score, +/-2 score for change in two of the characteristics.
  - Non-communicating Children's Pain Checklist-Revised (NCCPC-R): MCID = 0.25 SD

The MDRI will be calculated as the sum of scores from the components. Subjects will receive a score for each component of the MDRI listed above. A score of 0 will be given for a change in score less than the MCID. A score of +1 (improvement) or -1 (worsening) will be given for a change in score of  $\geq 1$  MCID and  $< 2$  times MCID. A score of +2 (improvement) or -2 (worsening) will be given for a change in score of  $\geq 2$  and  $< 3$  times MCID. A score of +3 (improvement) or -3 (worsening) will be given for a change in score of  $\geq 3$  times MCID. Seizures and movement disorder outcomes will be scored as described above.

3. Individual Clinical Response (ICR) – 5 most impactful clinical problems reported by the caregiver. Sum using 5-point Likert scale for each ICR element.

4. Gait: Qualitative assessment by physical therapist (i.e. improved, no change, worsened).
5. Stair climb/descent: Time and quality of movement.
6. Sleep Diary (1-week recall): Sum of the number of overnight awakenings, average duration of overnight awakenings, and duration of time for initial sleep onset at bedtime.
7. Stooling Survey.

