## 12.0 Data Management and Confidentiality

### 12.1 Subject Population(s) for Analysis

- ☐ Protocol-compliant population (PP): Any subject who received at least 85% of planned doses and attended all scheduled study visits.
- ☐ Safety population (SP): All subjects who receive any amount of treatment.

Safety population (SP) will be used for the primary analyses and the secondary analysis would be based on protocol-compliant population (PP) as part of sensitivity analyses.

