### **Secondary objective**

Outcome variables include Individual Clinical Response (ICR, 0~25: sum of the top 5 domains on a 5-point Likert scale), Gait analysis results (improved, no change, worsened), Stair climb/descent (time and quality of improvement), Sleep diary (sum of the number of overnight awakenings, average duration of overnight awakenings, and duration of time for initial sleep onset at bedtime), and Stooling survey results. For univariate analyses, similar statistical tests will be used as ones used for the primary objective, depending on the data type of the outcome for comparing two study periods. For multivariate analyses, mixed effect models (linear for continuous outcomes and non-linear such as multinomial logistic regression for categorical outcomes and Poisson (or Negative Binomial regression model, if over-dispersion is apparent) for count outcomes) will be used using 2-4 different time points (pre-observation, 8, 36 week treatment, post-observation periods) as within subject factor. Covariates such as sex and age will be considered in multivariate models if they are found to be statistically significant in changes of outcomes. Sub-scale analyses will be conducted if changes in the composite score are found to be statistically significant or are reached to a clinically meaningful boundary. We expect to have full data without any missing for all outcomes. However, in case of missing data, two imputation methods, i) last observation forward, ii) multiple imputation assuming missing at random, will be considered.

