## **14.0 Withdrawal of Subjects**

Subjects will be encouraged to complete the study; however, they may voluntarily withdraw at any time. If a subject is withdrawn prior to study completion, attempts will be made to schedule and conduct an Early Termination visit for medical assessment. If a subject cannot be contacted after 5 telephone calls and 3 letters/emails, they will be considered lost to follow-up.

Subjects who discontinue study medication (e.g. due to non-compliance, AEs, etc.) will be asked to remain in the study for follow-up per the study schedule to preserve the ability to perform an intent to-treat (ITT) analysis. If a subject or their legal guardian (as applicable) withdraws consent to participate in the study, attempts will be made to obtain permission to record survival and adverse event (malignancy, hospitalization for infection) data at the Week +44 study point.

Study drug will be discontinued in any subject meeting the following criteria for drug-induced liver injury:

- ☐ ALT or AST > 8x upper limit of normal (ULN)
- ☐ ALT or AST > 5x ULN for more than 2 weeks
- ☐ ALT or AST >3x ULN and (total bilirubin >2x ULN or INR > 1.5)
- ☐ ALT or AST >3x ULN with the appearance of fatigue, nausea, vomiting, right upper quadrant pain or tenderness, fever, rash, and/or eosinophilia (>5%)

Management of suspected drug-induced liver injury will be consistent with the FDA Guidance for Industry Drug-Induced Liver Injury: Premarketing Clinical Evaluation. Specifically, an increase of ALT or AST of >3x ULN will be followed by repeat testing within 48-72 hours of ALT, AST, alkaline phosphatase, and total bilirubin level. There will be inquiry made about symptoms. If symptoms persist or repeat testing shows ALT or AST >3x ULN close observation to determine whether the abnormalities are improving or worsening will be initiated as follows:

- ☐ Repeating liver enzyme and serum bilirubin tests two or three times weekly. Frequency of retesting can decrease to once a week or less if abnormalities stabilize or the trial drug has been discontinued and the subject is asymptomatic.
- ☐ Obtaining a more detailed history of symptoms and prior or concurrent diseases.
- ☐ Obtaining a history of concomitant drug use (including nonprescription medications and herbal and dietary supplement preparations), alcohol use, recreational drug use, and special diets.

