### **27.7 Dosing**

In this study anakinra subcutaneous (SC) will be administered at a dose level of 100 mg SC once daily. Anakinra will be administered every other day in patients who have severe renal insufficiency or end stage renal disease (defined as creatinine clearance < 30 mL/min as estimated from serum creatinine levels).

**Dose will be increased to 200 mg SC once daily**, with a maximum dose limit of 8 mg/kg/day, at **Week +8** if the change in at least one of the two most bothersome outcomes selected by the parents/guardians at the Day 1 visit has not improved by  $\geq$  the MCID as defined in Section 9.1. If the MCID is not achieved after 8 weeks on maximum trial dose of 200mg (max dose 8 mg/kg/day), **treatment with anakinra may be discontinued after a review and discussion between the study PI and subject's parent(s) of their child's individual results from all study outcome measures.**

**Dose will be increased to 200 mg SC once daily**, with a maximum dose limit of 8 mg/kg/day, at **Week +16** if the change in at least one of the two most bothersome outcomes selected by the parents/guardians at the Day +1 visit have worsened by  $\geq$  the MCID as defined in Section 9.1 between week +8 and week +16, after an improvement from Day +1 to week +8. If the MCID is not achieved after 8 weeks on maximum trial dose of 200mg (max dose 8 mg/kg/day), **treatment with anakinra may be discontinued after a review and discussion between the study PI and subject's parent(s) of their child's individual results from all study outcome measures.**

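### Children taken off anakinra for non-response from Week +16 stay on the visit schedule, so the Week +36 and Week +44 data mix on-drug and off-drug children under treatment and withdrawal labels

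*Protocol*

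**What the plan says.** Section 10.1 describes a 36-week treatment period followed by "another 8-week observational period to determine any effects of withdrawal from the treatment".

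Section 27.7 allows an earlier end to treatment. The condition is "If the MCID is not achieved after 8 weeks on maximum trial dose of 200mg" (capped by weight), in which case treatment "may be discontinued after a review and discussion between the study PI" and the parents. Escalation can take place at Week +8 or Week +16, so the permitted stop falls at Week +16 or Week +24.

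Section 14.0 says that subjects who discontinue study medication "will be asked to remain in the study for follow-up per the study schedule", so that an intent-to-treat analysis remains possible. In the Section 10.2 schedule, Weeks +20 and +24 carry safety laboratory tests only, so after Week +16 the next visit with outcome measures is Week +36. The early termination visit in the schedule's first footnote is for leaving the study, not for stopping the drug.

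Section 9.1 (Secondary Endpoints) defines change "from Day 0 to Week +36 (i.e. treatment phase") and relates adverse event incidence to 36 weeks of treatment. Section 12.2 (Secondary objective) fits mixed models with "2-4 different time points (pre-observation, 8, 36 week treatment, post-observation periods) as within subject factor".

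Section 12.1 leads with all subjects who received any treatment. The sensitivity set is "Any subject who received at least 85% of planned doses and attended all scheduled study visits".

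**The concern.** The time labels in Sections 9.1, 10.1 and 12.2 assume that every child is on anakinra until Week +36 and comes off it then. Sections 27.7 and 14.0 together produce children for whom that is untrue and who are nevertheless measured at Weeks +36 and +44. No passage separates the two groups.

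Three results are exposed:

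- **Withdrawal contrast.** The last 8 weeks are the only off-drug period after treatment. Including children already off drug blurs what the period was added to show.
- **Week +36 results.** They combine on-drug and off-drug values under a treatment label, and the adverse event incidence set against known anakinra frequencies counts a 16-week exposure as a 36-week one.
- **Compliant set.** On one reading of planned doses, it removes children because they did not respond, which favours the drug.

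**Working it through.** **The plan's own precision figure.** Section 12.3 gives a margin of error of half a standard deviation for a paired difference with 20 subjects. t(0.975, 19)/√20 = 0.468 SD, which agrees.

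**Time off drug** (visit weeks from Sections 10.2 and 27.7)

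| Stop | Off drug at Week +36 | Off drug at Week +44 |
|---|---|---|
| Week +16 | 36 − 16 = 20 weeks | 44 − 16 = 28 weeks |
| Week +24 | 36 − 24 = 12 weeks | 44 − 24 = 20 weeks |

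No outcome visit is scheduled at Week +24, so Week +16 is the main route.

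**Share of doses.** Once-daily dosing for 36 weeks is 36 × 7 = 252 doses. The 85% threshold is 0.85 × 252 = 214.2 doses, reached at about Week 30.6.

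- Week +16 stop: 112/252 = 44%.
- Week +24 stop: 168/252 = 67%.

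Both fail if planned doses means 252. Neither need fail if it means doses planned under Section 27.7 up to the stop.

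**Dilution of a pooled Week +36 to +44 change.** Let s be the share already off drug at Week +36. The protocol gives no value, so 10% to 50% is assumed. Suppose these children do not change on average over the 8 weeks.

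- Relative to the change in children still on drug, the pooled change is (1 − s): 90%, 70% and 50% for s = 10%, 30% and 50%.
- Relative to what the whole group would have shown had nobody stopped, suppose the stopped children would have had a fraction k of the others' withdrawal effect. The ratio is (1 − s)/[(1 − s) + s·k]. For s = 30% it is 0.70/1.00 = 70% with k = 1, 0.70/0.85 = 82% with k = 0.5, and 100% with k = 0.

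Non-responders plausibly have small k, so (1 − s) is the extreme of the second comparison.

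**Adverse events (illustration).** Assume a constant hazard giving 30% over 36 weeks on drug, s = 30% stopped at Week +16, and only on-drug events counted. The hazard is −ln(0.7)/36 = 0.00991 per week, the 16-week risk is 1 − exp(−16 × 0.00991) = 14.7%, and the observed proportion is 0.7 × 30% + 0.3 × 14.7% = 25.4%. The schedule records all adverse events to Week +44. If off-drug events are counted as well, the proportion mixes on-drug and background risk instead.

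**Selection in the compliant set, 252-dose reading (illustration).** Assume no drug effect, two independent symptoms, an MCID of 0.25 SD of the change, every child with neither symptom past the MCID stopped, and correlation r between the Week +16 and Week +36 changes.

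- Share retained: 1 − Φ(0.25)² = 1 − 0.5987² = 64%.
- Mean Week +36 change in those retained: r × φ(0.25)Φ(0.25)/0.64 = r × 0.36, which is 0.11 SD at r = 0.3 and 0.25 SD at r = 0.7. A simulation agrees. The full set gives 0.

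**Cost in precision of a subset.** With 18, 14 or 10 children the margin becomes 0.50, 0.58 or 0.72 SD, against 0.47 SD with 20.

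**The case against.** The strongest reply is that analysing all treated children regardless of stopping is deliberate and sound: Section 14.0 gives the intent-to-treat reason. For Day 0 to Week +36 this stands. The fault there is the treatment label and the absence of on/off-drug status, not the inclusion of these children. The reply does not reach the last 8 weeks, where no analysis policy can produce a withdrawal effect in a child with nothing to withdraw.

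It can also be said that such handling belongs in a statistical analysis plan. In part it does. But the protocol has itself fixed the sets, the time levels and the treatment label, and these do not fit its own Sections 27.7 and 14.0.

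Four stronger readings are tempting, and the document does not support them:

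- *The withdrawal effect is understated by a known 20% to 40%.* Stopping is discretionary and follows a review of all outcome measures, so the share is unknown and could be near zero. The loss is also smaller if non-responders would have shown little withdrawal effect.
- *The last 8 weeks are the trial's main control.* The named comparator is the 8-week observation period before treatment. No endpoint in Section 9.1 is a Week +36 to +44 change. The contrast follows from the purpose in Section 10.1 and the post-observation level in Section 12.2, which is one of 2 to 4 possible levels. Gait and stair climb are not scheduled at Week +44.
- *The compliant set necessarily drops non-responders.* That depends on how planned doses is read, and this set serves only sensitivity analyses.
- *The primary result is compromised.* The 8-week endpoints are read before any such stop.

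Finally, restricting the withdrawal contrast to children still on drug also selects on response. That is true, and the plan must say so.

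**Conclusion.** The point holds as an inconsistency between Sections 27.7 and 14.0 on one side and the labels and time levels of Sections 9.1, 10.1 and 12.2 on the other. A child stopped at Week +16 is 20 weeks off drug at Week +36, and that child's later change carries no information on withdrawal. This follows from the text alone.

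The consequence has a clear direction but no known size. The percentages above rest on an assumed share stopped, no mean change in children already off drug, and, for the second comparison, the effect they would have shown. The adverse event and selection figures are illustrations under their stated assumptions. The compliant-set problem is conditional on the 252-dose reading, and the protocol does not settle which reading applies.

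This should be corrected because it affects secondary results and the only off-drug period after treatment. It is not a threat to the trial's 8-week conclusions.

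**What to change.** **Section 12.2**

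- Estimate the Week +36 to +44 change in subjects still taking anakinra at Week +36, identified by last-dose date, and list the others separately. State that this subset is selected on response and tolerability, so that it describes withdrawal only in those still treated.
- Keep the all-treated Day 0 to Week +36 analysis, describe it as regardless of discontinuation, and show on/off-drug status at Week +36. Align the label in Section 9.1.
- Report 36-week adverse events per subject-week of exposure beside the proportion.

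**Section 12.1**

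- Count planned doses as those prescribed under Section 27.7 up to any stop that it permits, and judge dose and visit compliance up to the endpoint being analysed.

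**Cost.** Only analysis wording changes, with no added visits. Last-dose dates can be taken from the dispensing and return records (Section 27.4) and the four-weekly contacts, which ask about dose administration. The price is a withdrawal contrast with fewer subjects, a wider margin and a narrower, selected population. No change to the clinical stopping rule is proposed.

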## 10.2 Study Timeline/Schedule of Events

| Procedure                                              | Screening | Week -8                         | Day +1
±1 week | Weeks +2, +4,
+12, +20
and +24 k
±2 days | Week +36 a
±1 week | Weeks +8,
+16 and
+44
±1 week |
|--------------------------------------------------------|-----------|---------------------------------|-------------------|--------------------------------------------------------------|----------------------------------|----------------------------------------|
| Informed consent                                       | X         |                                 |                   |                                                              |                                  |                                        |
| Medical history b /Physical exam            | X         | X                               | X                 |                                                              | X                                | X                                      |
| Pubertal assessment (Tanner staging)                   |           | X                               |                   |                                                              | X                                |                                        |
| Concomitant medications c                   | X         | X                               | X                 |                                                              | X                                | X                                      |
| Pregnancy test                                         | X         | X                               | X                 |                                                              | X                                | X                                      |
| Vital signs, height, weight                            | X         | X                               | X                 |                                                              | X                                | X                                      |
| Child Sleep Health Questionnaire                       |           | X                               | X                 |                                                              | X                                | X                                      |
| Sanfilippo Behavior Rating Scale                       |           | X                               | X                 |                                                              | X                                | X                                      |
| Non-communicating Children's Pain Checklist-Revised    |           | X                               | X                 |                                                              | X                                | X                                      |
| Parent reported outcomes (PROMIS) d         |           | X                               | X                 |                                                              | X                                | X                                      |
| Seizure - parent assessment x 1 week                   |           | X h                  | X                 |                                                              | X                                | X                                      |
| Movement - parent assessment x 1 week                  |           | X h                  | X                 |                                                              | X                                | X                                      |
| Individual Clinical Response                           |           | X                               | X                 |                                                              | X                                | X                                      |
| Gait assessment                                        |           | X                               | X                 |                                                              | X                                |                                        |
| Vineland-III                                           |           | X                               |                   |                                                              | X                                |                                        |
| Stair climb                                            |           | X                               | X                 |                                                              | X                                |                                        |
| Sleep Diary – parent assessment x 1 week               |           | X h                  | X                 |                                                              | X                                | X                                      |
| Stooling Survey                                        |           | X                               | X                 |                                                              | X                                | X                                      |
| Safety labs (CBCD, BMP, LFT, lipid panel) i | X         | X                               | X                 | X                                                            | X                                | X                                      |
| Thyroid studies                                        | X         |                                 |                   |                                                              |                                  |                                        |
| Blood biomarkers                                       |           | X                               | X                 |                                                              | X                                | X                                      |
| Urine biomarkers                                       |           | X                               | X                 |                                                              | X                                | X                                      |
| Stool collection                                       |           | X                               | X                 |                                                              | X                                | X                                      |
| Genetic biomarkers (optional)                          |           | X                               | X                 |                                                              | X                                | X l                         |
| CSF collection (optional)                              |           | X                               | X                 |                                                              | X                                | X (week 44 only)                       |
| Whole Blood                                            |           | X                               | X                 |                                                              | X                                | X                                      |
| Anakinra e                                  |           |                                 |                   |                                                              |                                  | X (week 8 and 16 only)                 |
| Adverse events f                            |           | X                               | X                 |                                                              | X                                | X                                      |
| Contact for study follow up g               |           | Required every 4 weeks ± 7 days |                   |                                                              |                                  |                                        |

a If sponsor discontinues the study at any time, or a subject is discontinued from the study after week +8 and before week +44, an early termination visit will be done. Early termination visit procedures will be the same as for the week +44 visit.

b All procedures/intervention/surgery due to underlying MPS III will be recorded after informed consent is obtained, until week 44 or the Early Termination visit. If a subject is discontinued from the study prematurely, all procedures/intervention/surgery due to underlying MPS III will be recorded at the Early Termination visit.

c All medications (prescription, over-the-counter and herbal) and nutritional supplements taken 30 days prior to Screening and throughout the study should be documented.

d PROMIS surveys are the Autism Parenting Stress Index (APSI) and a customized Parent Proxy Fatigue – Short Form.

e The same injection site should not be used 2 days in a row, and should be rotated between the four injection sites (upper thigh, upper back of arm, abdomen or buttocks). Dose will be escalated at week 8 and 16, or decreased at any time, per protocol described in Section 27.7 Dosing.

f After written informed consent but before study treatment initiation, only SAEs associated with protocol-imposed interventions will be recorded. After study drug initiation, all AEs, SAEs, and pregnancy will be recorded until week 44 or the Early Termination visit. If a subject is discontinued from the study prematurely, AEs and SAEs will be recorded at the Early Termination visit.

g During these contacts, study staff will ask about dose administration and seek information on AEs and SAEs by specific questioning. Information on all AEs and SAEs should be recorded in the subject's medical record and on the AE eCRF.

h Diaries will be completed at week -6 to avoid the potential impact of travel on these outcomes.

i Plasma and serum samples collected and stored for PK and anti-drug antibody studies.

j Buffy coat will only be collected on Week -8, Day 1, and Week +36.

k Week +24 safety labs only if dose was increased at week +16.

